### Description of the Intervention

#### MINT-TLC Condition

This intervention is based on established clinical practice guidelines for prevention and treatment of HTN, which recommends weight loss (if overweight), regular physical activity, limiting and/or reducing sodium and alcohol intake, and eating a low-fat diet that is rich in fruit and vegetables [5]. Patients attend 10 weekly group classes over 12 weeks (intensive phase) followed by monthly, individual telephone-based MINT sessions for 3 months (maintenance phase). Makeup sessions are built in after session 4 and session 9 for group members who missed any of the previous sessions. The methodology, structure and the content of the group classes is patterned after PREMIER and Healthy Eating and Lifestyle Program (HELP) developed by Kumanyika et al. [44] The HELP program is based on the group counseling approach used in the Trial Of Nonpharmacologic interventions in the Elderly (TONE) trial, and was culturally tailored for African Americans. PREMIER is a comprehensive multi-component lifestyle program which incorporates the DASH dietary pattern [18]. The addition of three individual MINT sessions to this protocol was carefully chosen to mimic the structure of the two major trials that have tested the efficacy of comprehensive TLC in hypertensive patients [18,20]. The methodology, structure and content of the individual MINT sessions are patterned after our recently completed study in the same population [45].

##### Intensive Phase (Group Classes)

The group classes are conducted by Health Educators trained in behavioral counseling approaches. Each class lasts between 60 and 90 minutes, and is structured so that homework from previous sessions, a review of the goals participants set the previous week, feedback and trouble shooting for skill-building and new content is covered in each session. The sessions focus on developing skills, goal-setting and generating strategies for behavior change as well as support for relapse prevention. Each session follows a similar structure and includes the following components: 1) Overview of HTN and antihypertensive medications; 2) DASH eating plan 3) Goal setting and healthy living diaries; 4) Serving sizes, portion control and food labels (with emphasis on sodium monitoring); 5) Physical activity; 6) Building skills for meal planning and shopping; 7) Recipe modification and eating away from the home; 8) Stress Management; 9) Eating triggers and mindful eating; and 10) Planning for lasting change. The group classes are structured to be very interactive with patient input and smaller group activities that foster problem solving, support, and program ownership. The specific content of classes is shown in Table 1.

**Table 1 T1:** Major Content of TLC Intervention Sessions

Session	Content
**1. Getting Started & Blood Pressure Overview**	Introduction to the program. Education about blood pressure and hypertension. Discussion of risk factors for hypertension and behavioral approached to controlling hypertension.

**2. Medications**	Introduction to medications for HTN. Myths and Facts about HTN medications, tips for taking charge of medications, and understanding medication labels. Discussion of current medication taking behavior and goals for adherence. Introduction to the Medication Diary. At-Home Activity: Medication Diary.

**3. DASH Eating Plan & Introduction to Goal Setting**	Introduction to the DASH Eating plan. Discussion of DASH pyramid, food groups and servings. SMART goal setting for healthy eating goal. Introduction to Healthy Living Diary (food and activity diary). At-Home Activity: Healthy living diary, Medication diary.

**4. Food Labels & Sodium**	Discussion about reading food labels and nutrition facts. Facts about salt and sodium, and tips for how to lead a low sodium life. Revisiting healthy eating goal and introduction of rewards. At-Home Activity: Healthy living diary, Medication diary.

**5. Physical Activity & Stress Management**	Introduction to physical activity. Discussion of FITT guidelines, impact of exercise on HTN, finding time for physical activity. Physical activity goal setting. Discussion of stress and health. Quiet time activity. At-Home Activity: Healthy living diary, Medication diary.

**6. Serving Sizes and Portion Control**	Review of medications and DASH eating plan. Discussion about serving sizes, portion control and the plate method. Revisiting the physical activity goal. At-Home Activity: Healthy living diary, Medication diary.

**7. Meal Planning & Shopping**	Discussion of the buddy system and physical activity. Discussion of planning for meals and tips for shopping. Checking in on goal progress. At-Home Activity: Healthy living diary, Medication diary.

**8. Eating Triggers & Eating Awareness**	Discussion of eating triggers and eating awareness. Mindful eating activity. Revisit health eating goal. At-Home Activity: Healthy living diary, Medication diary.

**9. Specials Occasions, Eating Out &Recipe Substitutions**	Discussion of strategies for attending special occasions and eating out. Recipe substitutions. Revisit physical activity goal. At-Home Activity: Healthy living diary, Medication diary.

**10. Planning for Lasting Change**	Review of overall program content. Discussion of what worked with medication adherence. Adopting the attitude "It's not a diet it's a lifestyle." Discussion of physical activity throughout the year. Planning for lasting change activity.

##### Extended Phase (Monthly Individual MINT Sessions)

The individual telephone-based MINT sessions are conducted by the trained Health Educators. The goal of this phase is to help patients focus on problem solving, goal setting, and prevention of relapse with regard to each of the therapeutic lifestyle changes adopted during the intensive phase. The sessions focus on individual needs to tailor intervention strategies to the patient's personal context including social support, specific behavior change goals, problem-solving, and maintaining motivation during challenging situations. Each session assumes the following steps: 1) assessing the patient's motivation and confidence in engaging in a given behavior - physical activity, dietary restriction of sodium, increased intake of fruits and vegetables, stress management or adherence to prescribed antihypertensive medications; 2) eliciting barriers and concerns about adoption of each lifestyle modification; 3) summarizing in a non-threatening manner the 'pros' and 'cons' of the patient's concerns, thereby eliciting positive self-motivational statements about the behavior; 4) providing a menu of options to the patient based on the nature of barriers elicited from the patient; 5) assessing each patient's values and goals, in order to help the patient link current health behavior patterns to core values and life goals. The session ends with a global summary of what was discussed and a clarification of an action plan agreed upon. Each session lasts up to 30 minutes and is conducted with the aid of a standardized counseling script [45].

##### Monitoring treatment fidelity (intensity and the dose of the intervention)

Adherence to the intervention protocol is an important aspect of this study given its intensity. At the trial's inception, the Health Educators participated in a 3-day training that consisted of an overview of the behavioral framework of the intervention; the curriculum; and basic group facilitation skills taught through role-playing and didactic instruction. In addition, the Health Educators participated in a 2-day training on motivational interviewing skills including an overview of the basic principles of MINT techniques, development of problem-solving approaches, and practice sessions in the form of role-plays. Weekly meetings with study staff are held to discuss the sessions and plan for the subsequent week. Booster training sessions are also conducted monthly to minimize drift in MINT counseling skills.

All group and individual MINT sessions are audio-taped and used for two related purposes: (1) to provide feedback and ongoing training/supervision of the Health Educators and (2) systematic review for treatment fidelity. The relatively immediate review and use of the recordings serve to facilitate the feedback and coaching process to develop and maintain the skills of the individual Health Educators, a training approach that has proven to be most effective in previous studies of MINT [46]. Audio files are also archived to allow for systematic sampling of 30% of the MINT sessions, which will be coded in order to assess adherence to MINT principles using the Motivational Interviewing Treatment Integrity (MITI) scale [47]. The MITI scoring system was recently validated in an addiction treatment setting and found to have satisfactory inter-rater reliability and good convergent and discriminative validity [47]. In addition, this session archive will be used for future process evaluation to identify the important components of MINT used in the health behavior setting, as suggested by other researchers [48]. Finally, we record completion of the food diary and homework assignments as well as attendance of group classes and note the compliance and attrition rates.

### Description of the Control Condition/Usual Care

Patients randomized to the UC condition receive standard HTN treatment recommendations as determined by their physicians. In addition, they receive a 30-minute individual counseling session on therapeutic lifestyle modification, similar to PREMIER [16]. To match the MINT-TLC group for content of intervention material, those in the UC group also receive print versions of the intervention curriculum that is distributed in the group classes.

### Outcomes assessments

The primary outcome is change in SBP and DBP at 6 months. Secondary outcomes include: intake of fruits and vegetables; level of physical activity; percent change in weight; level of 24-hour urine sodium excretion; and proportion of patients with adequate BP control at 6 months. Study assessments for primary outcomes are completed at the baseline visit, 3 and 6 months; data collection intervals are given in Table 2. All assessments are performed by trained RAs and divided into three categories: (1) physiological and anthropometric measures, (2) self-report measures and (3) chart data. Table 2 summarizes the measures according to their timeline.

**Table 2 T2:** Study measures by modality

MEASURES	Baseline	3 Months	6 Months
**PHYSIOLOGICAL**			

Office BP Measurements	X	X	X

24-hour ABPM	X		X

Height, Weight, and Body Mass Index	X		X

Blood and Urine Specimen	X		X

**SELF-REPORT**			

Patient Demographics	X		X

Cognitive Screen for participants ≥ 60 yrs (CARE-DIAG)	X		

Diet (Food Frequency questionnaire)	X	X	X

Physical Activity (IPAQ Long Version)	X	X	X

**CHART DATA**			

Frequency of Clinic Visits and Medication Changes	X		X

Hypertension characteristics	X		X

Medical Comorbidity (Charlson Comorbidity Index)	X		X

### Primary Outcome

#### Blood Pressure

At baseline, 3 blood pressure (BP) readings are taken by a trained RA using an automated BP monitor (WatchBP Office Device; Microlife; Golden, CO) with the patient seated comfortably for 5 minutes before measurement, following AHA guidelines [49]. The average of the 3 readings is used as the measurement for each visit. Uncontrolled BP is defined as an average SBP ≥ 140 mm Hg or DBP ≥ 90 mm Hg. The criteria for those with co-morbid diabetes or kidney disease are SBP ≥ 130 mm Hg or DBP ≥ 80 mm Hg.

### Secondary Outcomes

*Dietary intake of fruits and vegetables *is assessed via a web-based graphical food frequency questionnaire (FFQ), which was adapted from the FFQ developed by Fred Hutchinson Cancer Research Center [50]. The instrument assesses how often, and in what amount patients eat a list of over 125 food items. The Graphical FFQ assesses portion size using photographs in order to get accurate responses.

*Physical activity *is assessed via a computerized version of the International Physical Activity Questionnaire (Long IPAQ) [51]. The Long IPAQ is a 32-item measure that allows for evaluating the amount of health-related vigorous and moderate-intensity physical activity as well as sedentary behaviors and physical activity limitations in adults over seven days. The number of hours and minutes per day participants report spending in various types of physical activity is multiplied by the average metabolic equivalent (METs) of each category and summed to calculate energy expenditure as kcal/kg/minutes/week.

*Height and weight *is measured without shoes and with lightweight clothes using a stadiometer and a validated digital scale (WB-800S Digital Medical Weight Scale; Tanita Corporation of America, Inc.; Arlington Heights, Illinois), respectively. All measurements are recorded to the nearest 0.1 cm and 0.1 kg. These data are used to calculate and determine the patient's body mass index (BMI). The difference in weight from baseline to 6 months serves as a measure of weight loss. Height is only measured at the baseline visit while weight is measured at baseline and 6 months.

A *24-hour urine sample *is collected at baseline and 6 months for analysis of urinary sodium excretion. Trained RAs provide instructions and a collection container in the clinic. Patients are also provided with a collection log on which they record the start and stop time; any missed voids, spills, and any other problems with the collection. Patients with inadequate collections (e.g., < 20 hours or < 500cc or > 24 hours) are asked to repeat the process.

*BP control *is defined as an average BP (based on 3 readings with automated BP monitor) that fulfills the JNC-7 criteria of SBP < 130 and DBP < 80 mmHg (patients with diabetes or chronic kidney disease); or SBP < 140 and DBP < 90 mmHg (for all other patients).

### Chart Extraction Data

All patients have their medical records reviewed at baseline and at 6-months by study staff. Chart data extraction includes duration of HTN, evidence of target organ damage, changes in prescribed antihypertensive medications dosages (this reflects the intensity of treatment). Others include frequency of clinic visits and reasons for visits; and use of other medications that are known to affect BP such as NSAIDS and hormone replacement therapy. Patients in this population have comorbid illnesses, which may affect BP levels - the primary outcome of this study. As such, we will use the Charlson Comorbidity Index (CCI)[52] to adjust for both the confounding effects of comorbidity on BP and their non-uniform prognostic impact on patients. The CCI is a weighted index for prospectively classifying comorbid conditions, which takes into account the number and seriousness of comorbid diseases.

Data on *patient socio-demographic characteristics *are also collected for description of the cohort and to examine effects of these factors on BP control. Variables include age, gender, education level, income, marital status, employment status, and health insurance status.

### Analysis

#### Sample Size and Power Analysis

The sample size is based on the number of patients required to provide adequate power to test the primary hypothesis of group differences in SBP and DBP. The power calculations assumed separate analyses of SBP and DBP; however, the use of multivariate analyses of variance (MANOVA) to examine the primary outcomes simultaneously, assuming that they are correlated was also considered. Power is expected to be greater with the use of MANOVA. However, we will use Full Information Maximum Likelihood estimation procedures for the primary analyses, thereby allowing us to include participants who do not complete the follow-up assessment in the analysis (on an intent-to-treat basis). The original power calculations were conservatively based on the number of participants who were anticipated to complete the follow-up assessment.

Based on our own clinical experience and estimates from other clinical trials in uncontrolled hypertensive patients,[16-18,20,53-57] we estimate that the cross-sectional standard deviations (SD) of SBP and DBP at baseline will be about 15/12 mm Hg. It was assumed that the SD at follow-up will be as much as 25% larger in the MINT-TLC group, and that the correlation between baseline and follow-up BPs will be 0.6 in the UC group and 0.4 in the MINT-TLC group (possibly as a result of heterogeneity of treatment response). Design effects of patients clustered within physicians has been found to be minimal in our experience; for example the intracluster correlation coefficient (ICC) was estimated to be 0.02 or less, and cluster sizes are relatively small. Clustering results in reduction in power and increased requirements for sample size. The variance inflation factor (VIF) used in power calculations involving clustering depends on the size of the cluster (number of patients treated by each physician) and ICC. Power calculations were examined in sensitivity analyses (not shown), assuming that heterogeneous variances may require modeling. The original power calculations were updated using actual data from the beginning of the trial. It was found that the average cluster size was 1.55 (SD = 1.39, ranging from 1 to 10 clusters and the total number of physicians was 92). The following assumptions were used in the power calculations: σ (population standard deviation) = 15 for SBP and 12 for DBP; α = 0.05, two-tailed; R = 0.9 (reliability); g = 2 (groups); n = 3 (waves, t = 0, 3 and 6 month); $s_{x}^{2}$(variance of time) = 0.125; inflation factor (IF) = 1+(clustersize-1)*ICC with clustersize = 1.55 and ICC = 0.01.

Thus, 100 subjects per group will provide 80% power to detect a 6 to 7 mm Hg differential change in SBP and a 5 to 6 mm Hg differential change in DBP, based on testing the Time (pre through post-intervention waves) × Group interaction in a mixed model, allowing for heterogeneous variances, serial correlations and modeling of design effects. As described below, analyses will be performed under an intent-to-treat design; therefore all patients, including those who drop out of the study will be invited back for the final assessments.

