**Methods/Design:**

This randomized controlled trial tests the effectiveness of a practice-based comprehensive therapeutic lifestyle intervention, delivered through group-based counseling and motivational interviewing (MINT-TLC) versus Usual Care (UC) in 200 low-income, African Americans with uncontrolled hypertension. MINT-TLC is designed to help patients make appropriate lifestyle changes and develop skills to maintain these changes long-term. Patients in the MINT-TLC group attend 10 weekly group classes focused on healthy lifestyle changes (intensive phase); followed by 3 monthly individual motivational interviewing (MINT) sessions (maintenance phase). The intervention is delivered by trained research personnel with appropriate treatment fidelity procedures. Patients in the UC condition receive a single individual counseling session on healthy lifestyle changes and print versions of the intervention materials. The primary outcome is within-patient change in both systolic and diastolic BP from baseline to 6 months. In addition to BP control at 6 months, other secondary outcomes include changes in the following lifestyle behaviors from baseline to 6 months: a) physical activity, b) weight loss, c) number of daily servings of fruits and vegetables and d) 24-hour urinary sodium excretion.

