#### Randomization

After completion of consent procedures and baseline data collection, a list of patient identification numbers is sent on a weekly basis to the data management team to be randomized in a 1:1 ratio to either the MINT-TLC or UC group. This project has a hierarchical study design with each patient nested within a primary care physician and patients are recruited at different times. Randomization is within primary care physician. Therefore, a randomization algorithm developed by the Data Coordinating Center at the Research Division of the Hebrew Home at Riverdale was used; this algorithm has yielded balanced groups for numerous studies. This randomization procedure is carried out using a SAS macro after a subject completes the baseline interview. A random number from 0 to 1 is used to determine the assignment group. The standard cut score is set at 0.5 for the first n subjects from the same provider, 4 for this study. Those who receive a random number between 0 and 0.5 are assigned to the control group and those with a random number greater than 0.5 are assigned to the intervention group. The balance between the groups within each provider is weighted carefully after the total number of subjects from a group reaches a pre-specified number. If more than the n subjects are randomized initially, the cut score for the next subject is equal to the ratio of the experimental group (n1) to the subjects already randomized (m) for that group (n1/m). The cut score is adjusted according to the previous number of subjects randomized.

Patients are informed of the results of randomization by an RA in person or by phone; at this time, the RA discusses the intervention/counseling session schedule, and answers any additional questions. Given the nature of the intervention, it is impossible to blind the RAs to the assigned condition. However, the dimension that the RA's knowledge of the assigned condition could possibly affect is the BP measurement - the primary outcome of this study. To reduce the potential for this bias, we use an automated BP device (WatchBP). Neither the RA nor the patients see the measurements during this process, which prevents the RA from influencing the BP readings.

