### Analysis of the Primary Aim

The primary pre-planned analyses are to examine SBP and DBP separately; however, if the two variables are correlated, MANOVA will be used to test the hypothesis that those assigned to MINT-TLC will, on average, exhibit greater 6-month decreases in SBP and DBP than those assigned to the UC condition. A mixed (fixed and random) effects model using SAS Proc Mixed is the method planned for use. Such models permit modeling heterogeneous group variances and serial correlations over time as well as the design effects of clustering. Moreover, the use of the missing data algorithms within the mixed procedure permits the inclusion of all individuals with at least one wave of data. The primary test concerns the Group × Time interaction, and the resulting F-test will provide the primary "intent-to-treat" test of the hypothesis. If this is statistically significant at the two-tailed α = 0.05 level, the magnitude of the treatment effect will be estimated with 95% Confidence Interval (CI), separately for SBP and DBP. The expectation is that the randomization of patients to treatment arm and the absence of significant selection and/or attrition biases will obviate the need for any covariates in the analysis. This has been the normative experience of the data coordinating center in over 100 randomized trials. However, in the unlikely event that imbalances are identified, propensity score analyses or other methods will be used to condition on the covariates. The predicted values of those analyses will be included as covariates together with the group by covariate interactions in the model. This procedure is most often applied in quasi-experimental and observational studies.

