### Mode of Intervention Delivery

The potential for low patient participation rates in the group classes and MINT counseling sessions is another real-world challenge encountered in this study. We have adopted several strategies to facilitate high participation rates, including offering classes in the clinic; determining a cohort's class schedule based on the most frequently selected time and date chosen by patients during the eligibility screen visit; and offering Saturday classes and make-up classes on an alternate day and time. Despite these efforts, approximately 50% of patients attend the weekly group classes, of which 35% have attended 9 to 10 of the classes (total of 10 classes). Most frequent reasons for low group class attendance include patients' reporting another time commitment or conflict, being too ill to travel to the classes on a weekly basis, inability to reach the patient to remind them of the class time and location, and patient's having difficulty arranging for paratransit services (e.g., Access-a-Ride) to bring them to the clinic on off hours (evenings and weekends).

Similarly, approximately 50% of patients have received the telephone-based MINT sessions to date. To increase the completion rate, Health Educators make four call attempts to each patient at different times of the day over a 2-week period before they are considered a missed appointment. However, it is often difficult to reach patients by phone as many participants have intermittent use of their phones and their numbers change frequently. Letters signed by the Health Educators are also sent to patients with the study coordinator's phone number. It is noteworthy that 47% of patients that attended at least 5 of the group sessions have completed at least 1 MINT session. Further, 42% of patients that attended no classes have completed at least 1 MINT session, which suggest that this intervention modality may be effective in certain subgroups.

Despite the many challenges we have experienced to date, implementation of this trial has presented us with the unique opportunity to question which intervention approaches work in real-world settings, where patients have competing priorities and the demands of life often outweigh the perceived benefits of participation. Based on our experiences implementing the TLC-Clinic trial, we would recommend future researchers conduct a formative evaluation prior to implementing the trial at the participating clinic sites.

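### MINT-TLC is given in class cohorts in one arm only, yet physician is the only cluster unit the plan defines; if classmates' outcomes correlate, the primary test is anti-conservative and the power statement optimistic

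*Protocol article*

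**What the plan says.** **Delivery.** Under Intensive Phase (Group Classes), the article says: "The group classes are structured to be very interactive with patient input and smaller group activities that foster problem solving, support, and program ownership". Under Mode of Intervention Delivery, one strategy to raise participation is "determining a cohort's class schedule based on the most frequently selected time and date chosen by patients during the eligibility screen visit". MINT-TLC patients therefore belong to class cohorts with a common timetable. The control arm has no counterpart (Abstract, Methods/Design): "Patients in the UC condition receive a single individual counseling session on healthy lifestyle changes".

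**Clustering in the design and power calculation.** The Randomization section describes "each patient nested within a primary care physician" and randomises within physician. Sample Size and Power Analysis defines the cluster by the number of patients per physician and says: "Design effects of patients clustered within physicians has been found to be minimal in our experience". It uses a mean cluster size of 1.55 and an ICC of 0.01. With 100 patients per group it claims 80% power for a differential change of 6 to 7 mm Hg in SBP and 5 to 6 mm Hg in DBP.

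**Clustering in the analysis.** Analysis of the Primary Aim says that mixed models can handle heterogeneous group variances and serial correlation "as well as the design effects of clustering". It names no cluster unit. Neither class cohort nor Health Educator appears anywhere as a source of correlation.

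**The concern.** Physician clusters are small and are split between the arms by the randomisation, so physician effects largely cancel in the treatment contrast. Class cohorts lie wholly inside one arm, so a class effect does not cancel. Classmates share a Health Educator and sessions designed to make members support one another, which is a plausible source of positive correlation.

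If that correlation exists and the model omits it, the variance of the MINT-TLC mean is understated. The primary F-test then rejects too often and the confidence interval is too narrow, an error that favours a false claim of benefit. Arm-specific variances do not cure this, because they leave classmates independent of each other. The power statement would be optimistic for the same reason.

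**Working it through.** **Inputs from Sample Size and Power Analysis:** SD 15 (SBP) and 12 (DBP); follow-up SD up to 25% larger in MINT-TLC; baseline to follow-up correlation 0.6 (Usual Care) and 0.4 (MINT-TLC); 100 per group; two-sided alpha 0.05; 80% power. **Assumed, because the article does not give them:** class size m and class ICC.

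**1. Reproduce the stated figure.** Variance of the SBP change:
- Usual Care: 2 × 15² × (1 − 0.6) = 180
- MINT-TLC: 15² + 18.75² − 2 × 0.4 × 15 × 18.75 = 351.6

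Detectable difference = (1.960 + 0.842) × √[(180 + 351.6)/100] = 6.46 mm Hg, or 6.48 with the 1.0055 factor. For DBP the variances are 115.2 and 225.0, giving 5.17 mm Hg, or 5.18 with the factor. Both lie inside the stated ranges, so the claim is reproduced with no allowance for classes.

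**2. Add class clustering in MINT-TLC only.**
- Design effect: DE = 1 + (m − 1) × ICC
- Total variance: V = 180 + 351.6 × DE
- SE ratio: r = √(V/531.6)
- Type I error of the naive test: 2 × [1 − Φ(1.96/r)]
- Detectable difference: 2.802 × √(V/100)

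SBP, m = 10, physician factor left out (it adds about 0.02 mm Hg):

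| Class ICC | DE | V | SE ratio | Type I error | Detectable SBP difference | Power at 6.46 mm Hg |
|---|---|---|---|---|---|---|
| 0.01 | 1.09 | 563.2 | 1.03 | 5.7% | 6.65 | 78% |
| 0.02 | 1.18 | 594.8 | 1.06 | 6.4% | 6.83 | 75% |
| 0.05 | 1.45 | 689.8 | 1.14 | 8.5% | 7.36 | 69% |
| 0.10 | 1.90 | 848.0 | 1.26 | 12.1% | 8.16 | 60% |

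For classes of 5, the type I error over the same ICCs runs from 5.3% to 8.1%.

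**3. Compare with the factor the plan uses.** At the plan's own physician ICC of 0.01, classes of 10 raise the total variance by 563.2/531.6 − 1 = 6.0%. The physician factor raises it by 0.55%.

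**4. Find where the stated range fails.** Keeping the 1.0055 factor, the SBP difference reaches 7 mm Hg when V = (7/2.802)² × 100/1.0055 ≈ 620.9, so DE = (620.9 − 180)/351.6 ≈ 1.25. That is an ICC of about 0.25/9 = 0.028 for classes of 10, or 0.25/5 = 0.05 for classes of 6. For DBP and 6 mm Hg the limit is DE ≈ 1.52.

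**5. Allow for attendance (illustration).** Suppose the class effect acts only on a random half of each cohort. An ICC of 0.05 among attenders becomes 0.25 × 0.05 = 0.0125 over all assigned pairs. With m = 10, DE = 1.11, type I error is about 5.9% and the detectable SBP difference about 6.70 mm Hg.

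Steps 1 to 5 use a two-point change score and a normal test. The planned test is a three-wave Group × Time F-test, so these are approximations to its behaviour.

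**The case against.** The strongest reply is that the documents support the omission and the direction of the error, but not its size. No class size, number of cohorts or class ICC is given. About half the patients attend the classes, and the maintenance phase is individual and by telephone, so the ICC over all assigned patients could be small. With classes of 10 and an ICC of 0.01 to 0.02, the detectable SBP difference stays within the stated 6 to 7 mm Hg. All of this stands.

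A reader might infer that the standard errors are certainly too small and the 80% power claim wrong. The documents do not show that: both statements need a positive class ICC, and the power range fails only above the design effects in step 4.

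A reader might also infer that the plan rules out a class effect. It does not. The analysis wording is general, and a condensed article may leave the random-effects structure to a fuller document. What the article does fix is the cluster unit for design and power, and that unit is the physician alone.

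Nor is calendar period a one-arm cluster, since Usual Care patients are also enrolled over time. The case rests on shared classmates, sessions and Health Educator.

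**Conclusion.** The point holds in conditional form. MINT-TLC is partially nested, and the only cluster unit defined is the one with little influence on the treatment contrast. A primary test that ignores class is anti-conservative at any positive class ICC. For assumed classes of 10 and ICCs of 0.01 to 0.05, the type I error is about 5.7% to 8.5% and the detectable SBP difference about 6.65 to 7.36 mm Hg. An ICC of 0.10 would be worse, but it is the least supported case given the attendance. Nothing in the article justifies taking the ICC as zero in a programme built on group support. Severity: should-fix. The consequence is plausible and the remedy feasible, but the size is not established.

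**What to change.** **Primary model.** Add to the Proc Mixed model a random effect for assigned class cohort, in the MINT-TLC arm only and acting at the follow-up visits, because classes have not met at baseline. Code Usual Care patients as singletons with no class variance. Use arm-specific residual variances and Kenward-Roger or Satterthwaite degrees of freedom.

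**Definition of cohort.** Use the cohort as scheduled, not as attended. Attendance records alone will not do: some patients attended no class, and make-up sessions blur membership. Every MINT-TLC patient needs a recorded assigned cohort.

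**Power statement.** Give the detectable differences over a stated range of class sizes and class ICCs, alongside the physician factor.

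**Cost.** No new patients or visits are needed, but assigned cohorts must be recovered from the scheduling records. The interval becomes somewhat wider and degrees of freedom are lost. With 100 MINT-TLC patients in classes of 10 there would be only about 100/10 = 10 cohorts, so the class variance would be estimated imprecisely.
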